### 2.3. Recruitment

The recruitment of healthcare professional, patients and caregivers will last 7 months. Healthcare professionals will be recruited during the first 4 months by each pilot site using a convenience sampling based on their individual profiles. The healthcare professionals will be contacted via email, letter, or face-to-face meeting to provide them with initial information about the ADLIFE intervention. Healthcare professionals consenting to participate will be recruited.

Once healthcare professionals have been recruited and trained in the use of the ADLIFE intervention, each pilot site will identify a tentative target patient population fulfilling the eligibility criteria from EHR. After a validation process conducted by the healthcare professionals, a final target population will be defined.

The intervention and control group will be recruited from the final target population during the last 2 months. Candidates for the intervention group will be recruited by healthcare professionals or research assistants according to the inclusion/exclusion criteria. They will be contacted by email, post, phone, or face-to-face meetings, and provided with information describing the ADLIFE intervention, their expected role, and their required ICT skills. Patients participating in the intervention will sign an informed consent and will receive ADLIFE intervention training.

Patients in the intervention group may appoint an informal caregiver who will participate with them in ADLIFE in order to assist them with ICT management and self-management empowerment of their disease. Informal caregivers will sign an informed consent to participate in the intervention, and a second informed consent to access their corresponding patient’s data. They will receive ADLIFE training together with the corresponding recruited patient they care for.

In the event of a participant’s drop-out of the project, their previously collected data will be retained, unless otherwise stated, and analyzed under the intention-to-treat principle. Drop-out reasons will be defined as: (i) death, (ii) not interested in the intervention anymore, (iii) too time-consuming, (iv) technology issues, (v) declaring lack of help from their informal caregiver, (vi) institutionalization, which implies a change of healthcare professional, and (vii) no response. In the case of healthcare professionals, any position change will also be considered as drop-out reason. Informal caregivers will automatically drop-out of the project if their patients do so.

After removing the intervention patients from the final target population, a target control population will be identified. Control group patients will be retrospectively selected based on the afore-mentioned matching techniques (see Section 2.1.1.) from the target control population. No signed informed consent will be needed since anonymous data will be extracted from EHR by the pilot sites. Intervention patients withdrawing from the intervention will not be eligible for the control group. The recruitment process is described in Figure 2.

### 2.4. The ADLIFE Intervention and Standard of Care

The ADLIFE intervention consists of the deployment and use of the ADLIFE toolbox by patients, informal caregivers, and healthcare professionals in the afore-mentioned pilot settings.

The ADLIFE toolbox involves two interconnected platforms. Patients will use the Patient Empowerment Platform (PEP), and healthcare professionals will be assisted by clinical decision support services within the Personalized Care Plan Management Platform (PCPMP). Patients participating in ADLIFE will have a personalized care plan, created in PCPMP, which will be developed and managed together with their healthcare professionals. PCPMP will be used in integration with the clinical sites’ ICT systems to create patient care plans based on each patient’s baseline and most recent clinical data, following clinical evidence. PEP will facilitate the patient’s independence and self-management by presenting their personalized goals, activities, and educational materials, collecting their observations and questionnaires, and providing real-time interventions tailored to the patient’s lifestyle.

The main task of patients and their informal caregivers will be to use the PEP as part of their healthcare management process together with their healthcare professionals. The ADLIFE intervention will consider the health-related outcomes relevant for the patient in actual health service planning and evaluation. By identifying the outcome that will be responsive to each measure, professionals and patients will have the chance of reviewing the health-related outcomes, and of jointly choosing the activity, objective or goal that boosts the desired one. The health-related outcomes will be reflected as labels that bind every activity, goal, and/or indicator included in a care plan. The labelling mechanism has been co-created with healthcare professionals and automated to enable health-related outcome tracking over time and over a wide spectrum of patients.

The control group follows the SoC according to the pilot site organizations’ criteria. Since pilot sites belong to different health care systems, information on SoC was derived from semi-structured interviews with three stakeholder groups, 5–7 persons in each group [21].

### 2.5. Outcomes

The set of health-related outcomes grouped around relevant domains for the ADLIFE target population was defined following the International Consortium for Health Outcomes Measurement (ICHOM) methodology (see online the Supplementary File S2 for details) [23,24]. The health-related outcome set provides a consensual definition of desired end results for both the outcome-based care planning and for the project evaluation. The framework groups each of the primary and secondary outcomes by the broad health-related outcome to which it is responsive. Figure 3 shows the Health-Related Outcome set for people over 55 years old with severe heart failure and/or COPD. The conceptual data framework identifies the relevant health areas (outer ring).Each health outcome area comprehends multiple dimensions (inner ring).

Besides health-related outcomes, implementation-related outcomes including barriers/facilitators related to the implementation process, technology acceptance and adoption, and contextual factors for further exploitation to later scaling-up will also be assessed. To define the variables of interest, a framework for implementation assessment was developed (see Figure 4) which is based on a human, organization, and technology-fit (HOT-fit) framework as a Health Information System evaluation framework [25], and is complemented with the intervention, process, and outer setting of the Consolidated Framework for Implementation Research (CFIR) [26]. Together, these frameworks provide a structured and systematic way to identify constructs influencing the implementation of ADLIFE on different levels.

#### 2.5.1. Primary

The primary outcome will be the number of ER visits during the 9-month follow-up. The ER visits regularly become a crucial point in healthcare systems when care is poorly coordinated. A high number of ER visits has been associated with functional decline and mortality [27]. In this context, existing evidence suggests that frequent ED users are at-risk patients for whom interventions may improve health outcomes [28,29]. Then, this primary outcome, defined as the main effectiveness outcome, is a proxy of the appropriateness of care in real-life settings for patients with ADC, and consequently, a gain in health-related outcomes [27,28,29]. ER visits will be collected from the EHR.

#### 2.5.2. Secondary

The secondary outcomes will be assessed on patients, caregivers, and healthcare professionals.

Patients will be assessed on:Patient-Reported Outcome Measurements (PROMs):Health-related quality of life (EQ-5D-5L) [30];Mood/emotional health (HADS—Hospital Anxiety and Depression Scale) [31];Activities of daily living (Lawton scale, Barthel Index, Kansas City Cardiomyopathy Questionnaire score, COPD assessment test score) [32,33,34,35];Complexity (Modified Medical Research Council—mMRC—Dyspnea Scale) [36].
Technology acceptance and future adoption of the ADLIFE intervention (the Unified Theory of Acceptance and Use of Technology, UTAUT) [37];Resource use and their associated costs will be also assessed on patients [38] (see data collection guide 2 in Supplementary File S4);Caregiver will be assessed on:Burden (Zarit Burden Interview, ZBI) [39];Mental well-being (Warwick-Edinburgh Mental Wellbeing Scale, WEMWBS) [40].Healthcare professionals will be qualitatively assessed on:Perceived coordination among settings;Quality of the integration of care;Decision making process;Working conditions.All stakeholders will be qualitatively assessed on:Perceived communication;Satisfaction with accessibility, security, and personalized care plans;Barriers/facilitators related to the implementation process.

Within the scope of the implementation assessment, contextual factors focusing on local technological, organizational, and human factors, will also be qualitatively assessed before and one year after the start of the intervention in a sub-group of different stakeholders including physicians, general practitioners, nurses, health coordinators, IT staff, and hospital CEOs [41].

### 2.6. Sample Size

The sample size was calculated using the number of ER visits as the main primary outcome. In order to detect an effect size of 0.6 ER visits per year, with a standard deviation of 1.2 with a 5% level of significance, a 90% of statistical power set, assuming a conservative intra-cluster correlation coefficient of 0.06 (each pilot site defined as a cluster) and a drop-out rate of 30%, 1692 patients will be required (846 per branch) across pilot sites.

For the qualitative approach, a purposeful sampling will be used to select the participants, recruiting those participants who might provide in-depth and detailed information about the ADLIFE intervention. The pre-intervention interviews for the implementation assessment will involve: one medical director, six healthcare professionals (two physicians, two general practitioners, and two nurses), and two IT staff for each pilot site. The post-intervention interviews will be structured in the same way, adding three to six patients and three to six informal caregivers for each site.

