#### 2.9.1. Effectiveness Assessment

A mixed assessment strategy will be performed using quantitative and qualitative methods.

For the quantitative approach, first a descriptive analysis followed by univariate statistical tests will be conducted. The effect of the intervention will then be assessed by generalized mixed models for longitudinal data. Linear models will be used for continuous variables and logistic models for dichotomous variables. Given the hierarchical structure of the data where patients are nested in pilot sites, the latter will be included as random effect to control the models by the variability across sites. In order to consider the different time of follow-up of each participant, all models will be adjusted by this factor, i.e., the time of follow-up will be included as a covariable. All models will also be adjusted for potentially confounding factors. Since healthcare services data are usually characterized by being discrete, zero-inflated counts and right-skewed, special attention will be paid to the selection of the distribution which best fits the data. In all quantitative analyses, we will use an intention-to-treat approach and set the level of significance at *p* < 0.05.

For the qualitative approach, a two-step analysis will be conducted. The pilot sites will first perform a content analysis in their own languages [44], based on a systematic approach to determine trends and patterns within the text, and will organize and identify topics and their relationships. For each identified topic, a comprehensive set of quotes will be transcribed to ensure comparability across regions. Then, in a second step, an aggregate cross-country analysis to assess the validity of the results, by comparing the main results among the pilot sites and the different stakeholders, will be conducted by the evaluation coordinator. The COREQ Checklist (Consolidated criteria for Reporting Qualitative research) [45] for quality assurance will be followed.

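### Section 2.6 inflates the sample size about sevenfold for clustering by site although both arms come from the same sites, and 846 per arm does not follow from the stated inputs with seven sites

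*Protocol article*

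**What the plan says.** Section 2.6 (Sample Size) aims to "detect an effect size of 0.6 ER visits per year, with a standard deviation of 1.2", "with a 5% level of significance" and "a 90% of statistical power set". It then proceeds by "assuming a conservative intra-cluster correlation coefficient of 0.06 (each pilot site defined as a cluster) and a drop-out rate of 30%, 1692 patients" in total, 846 in each arm. It gives neither a cluster size nor a design effect.

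Section 2.1 lists seven pilot sites in six countries. Under section 2.3 each site builds its own target population from its health records, and "The intervention and control group will be recruited from the final target population during the last 2 months". Controls are matched from what is left once the intervention patients are removed. In section 2.9.1 patients are nested in sites, and "the latter will be included as random effect to control the models by the variability across sites".

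**The concern.** The usual factor 1 + (m − 1) × ICC answers one question: how much information is lost when everyone at a site is in the same arm, so that differences between sites are mixed up with the treatment contrast. Sections 2.3 and 2.9.1 describe another structure. Each site contributes patients to both arms, and the model carries a site effect. A site with generally high emergency-room use then raises both arms, and that shift largely disappears from the difference.

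Two things are at stake. First, the stated 90% power rests on a variance that the design does not have. Second, a reader who puts the stated inputs and seven sites into the standard formula does not get 846. What the within-site comparison does leave exposed is variation of the treatment effect from site to site. A site ICC does not measure that, and section 2.6 does not mention it. The Discussion (section 3) does concede that differences between health systems could distort the overall effect.

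**Working it through.** **Inputs (section 2.6):** difference 0.6, SD 1.2, alpha 5% (sidedness not stated; two-sided taken), power 90%, ICC 0.06, drop-out 30%, 846 per arm. Section 2.1: seven sites. Section 2.1.1: one control per intervention patient.

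**1. Size without clustering.** n0 = 2 × 1.2² × (1.960 + 1.282)² / 0.6² = 84.06 per arm, or 86 using the t distribution. Ranges below run from the first to the second.

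**2. What 846 implies.** 846 × 0.7 = 592.2 evaluable per arm.
- Design effect: 592.2 / 84.06 = 7.05, or 592.2 / 86 = 6.89.
- Cluster size per arm: 1 + 6.05 / 0.06 = 102, or 1 + 5.89 / 0.06 = 99.

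**3. Does 846 follow from seven sites?** For k clusters per arm the self-consistent evaluable size is n = n0 × (1 − ICC) / (1 − n0 × ICC / k). For a given cluster size m it is n0 × [1 + (m − 1) × 0.06]. Each is divided by 0.7.

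| Reading | Design effect | Enrolled per arm |
|---|---|---|
| Seven clusters per arm, self-consistent (m about 40 to 44) | 3.36–3.58 | 404–439 |
| m = 592.2 / 7 = 84.6 evaluable per site per arm | 6.02 | 722–739 |
| m = 846 / 7 = 120.9 enrolled per site per arm | 8.19 | 984–1,007 |
| Six clusters per arm, self-consistent | 5.90–6.71 | 708–825 |
| m = 100 (not stated in the article) | 6.94 | 833–853 |

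No seven-site reading gives 846. Six clusters with the t-based n0, or an unstated cluster size near 100, comes close.

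**4. Both arms at each site, effect common to all sites.** If the arms are balanced within sites and the site effect is stable, the variance factor is 1 − ICC = 0.94.
- Needed: 84.06 × 0.94 = 79 evaluable per arm; 79 / 0.7 = 113 enrolled.
- At 592 evaluable: SE = 1.2 × √(2 × 0.94 / 592) = 0.0676. Power for 0.6 exceeds 99.9%. The difference detectable with 90% power is 3.242 × 0.0676 = 0.22.

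**5. Effects that differ between sites.** Let tau be the SD of the site-specific effects. Then var = 2 × SD² × (1 − ICC) / n + tau² / 7, tested with 6 degrees of freedom. The article gives no tau, so the values below are assumptions. As a yardstick, the plan's own ICC and SD imply a between-site SD of the outcome of √0.06 × 1.2 = 0.29.

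| Assumed tau | SE at 592 per arm | Power for 0.6 |
|---|---|---|
| 0.20 | 0.101 | 99.8% |
| 0.29 | 0.129 | 97% |
| 0.35 | 0.149 | 92% |
| 0.40 | 0.166 | 85% |

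Power crosses 90% at a tau of about 0.36.

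**The case against.** **Cancellation may be incomplete.** The design is called non-concurrent, and the Discussion speaks of a control period. If the arms at a site come from different periods, only the stable part of the site effect cancels. With an assumed correlation r between a site's two periods, and 592 / 7 patients per site per arm, the variance factor is 0.94 + (592 / 7) × 0.06 × (1 − r). That is 0.94 at r = 1, about 2.0 at r = 0.8 and about 3.5 at r = 0.5. Nor does the article say outright that matching is done within site. This objection stands: 0.94 is the best case, and some inflation can be defended. These factors are still well short of seven, and section 2.6 argues none of them.

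**The missing cluster size may be condensed detail.** A journal article may leave the cluster size to the full protocol, and six clusters would fit the six countries (846 = 6 × 141). That is plausible but unproven. It would explain the figure without reconciling it with the stated unit, which is the pilot site, of which there are seven.

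**The consequence is small.** On the seven-cluster logic itself, 592 evaluable per arm (m = 84.6) gives about 94% power by normal approximation, or about 90% with 12 degrees of freedom. This also stands.

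**Two stronger readings are not supported.** A reader might infer that the trial is under-powered. That needs effects to vary across sites more than the plan's own ICC says the outcome varies, and nothing in the article points to such a value. A reader might also infer that drop-out inflation should not apply to retrospectively selected controls. But section 2.3 counts death and institutionalisation as drop-out, both can happen to controls, and 1:1 matching leads to equal arms.

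**Conclusion.** The point holds on two counts. An inflation of about sevenfold belongs to a design that assigns whole sites, and this one compares patients within sites. And 846 per arm does not follow from the stated inputs with seven sites.

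The error is mainly conservative. For a common effect of 0.6 with SD 1.2, the target is several times what the comparison needs (113 against 846 enrolled per arm in the best case). That best case assumes arms roughly balanced within sites and a site effect stable across periods. The plan's 90% figure is therefore not wrong in a way that endangers the trial, but its stated basis does not describe this trial. It also says nothing about variation of the effect between sites, the component that enrolling more patients at the same seven sites cannot reduce. The change is worth making and is not urgent.

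**What to change.** Keep the enrolment target and rewrite the first paragraph of section 2.6:

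- State the cluster count, the cluster size and the design effect behind 846. If six clusters were used, say so and reconcile that with the seven pilot sites; otherwise correct the seven-site arithmetic.
- Restate the power at 846 per arm (592 evaluable) on the within-site comparison, for example with var = 2 × SD² × (1 − ICC) / n + tau² / 7 and 6 degrees of freedom.
- Show it over a range of tau labelled as an assumption (99.8% at 0.20, 97% at 0.29, 92% at 0.35, 85% at 0.40), with the implied between-site SD of 0.29 as the yardstick.
- Say whether controls are matched within site and over which calendar period. If the periods differ, add an allowance for site-by-period variation.

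The cost is one rewritten paragraph and a short calculation. Enrolment and the drop-out allowance stay as they are.

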### 2.7. Data Collection

A data collection guide including a codebook and a template will be provided to pilot sites to conduct the quantitative data collection on socio-demographic, clinical, economic, and usability variables. Variables will be observed at baseline and at endpoint, except for resource use which will be measured during the 9-months before and after the baseline, and except for the usability variables which will be measured at endline. Data collection flows are shown in Figure 1. Data will be collected from three data sources: the EHR, Qualtrics questionnaire for technology acceptance completed by participants, and the on FHIR repository [42]. For the effectiveness and socio-economic evaluation, each pilot site will provide its corresponding dataset to the evaluator site to be merged into a single data space. Data collection guides 1 and 2 in the Supplementary File S3 and S4 show comprehensive variable lists to be collected. For the technology acceptance and adoption, pilot sites will communicate the online questionnaire links to the participants and the data will be collected. A data collection guide for the technology acceptance and adoption evaluation can be found in the Supplementary File S5.

For the qualitative work, semi-structured interviews will be conducted on patients, informal caregivers, healthcare professionals, managers, and IT staff. A detailed protocol with the data collection guide and templates to be used for summarizing the data interviews will be circulated across pilot sites. Interviews at each pilot site will be conducted in the corresponding national language, and will preferably take place face-to-face, or virtually if necessary (telephone or videoconference). The interviews will be audio recorded and verbally transcribed to a structured template. For effectiveness assessment, data from interviews will be collected after follow-up period, whereas for implementation assessment a pre-post approach will be followed.

### 2.8. Data Management

A robust approach to data protection and data management is adopted prior to any contact with patients or their health data. This approach is described in the Data Management Plan (DMP) [43]. The DMP describes the data protection roadmap for each of the five categories of patient level data (mock healthcare data, training healthcare data, control healthcare data, intervention healthcare data and patient/HCP reported data). At a glance, the DMP presents the data processing and flows that will largely take place within each of the seven pilot sites, to identify patients who match the eligibility criteria for the ADLIFE intervention, and then how these data will be processed including pseudonymization and anonymization steps, before being made available for wider consortium use. This wider use includes the design and development of technical components, and the training and validation of artificial intelligence algorithms. The anonymization process begins with the classification of the sensitivity of those variables that are essential for the purpose of the study. The protection criteria established include the anonymization of direct identifiers using hash algorithms, and the anonymization of indirect identifiers using micro-aggregation and temporal perturbation, reducing the risk of re-identification of the information as a whole to 5%. It will therefore be ensured that, within reasonableness and within the procedures adopted, no personal data or datasets can be associated to any person, within a reasonable time.

The DMP also focuses on the formal Data Management Plan template published by Horizon 2020. This mostly confirms the intention of the project to make available some open research data at the end of the project, and how it intends to comply with the FAIR principles. The DMP therefore, sets the principles to enable a privacy-by-design approach to data sharing by balancing the benefits of using personal health data with a range of risk-management controls.

